##### Clinical outcomes

- Thickness of melanomas biopsied in secondary care clinics;

- 5 year melanoma incidence and mortality among trial participants collected through the Eastern Cancer Registration and Information Centre (ECRIC).

##### Clinician outcomes

- Accuracy of Index of Suspicion scale;

- Confidence and attitudes of Lead Clinicians towards the MoleMate intervention will be assessed 2 weeks after trial set-up and at trial completion using a modified measure based on the Theory of Planned Behaviour [23];

- Learning effects: it is possible that the MoleMate training programme, and using the MoleMate system in practice, may improve the Lead Clinicians' accuracy to assess pigmented lesions clinically and thereby affect management of lesions in both groups. We will therefore examine potential contamination effects by comparing the appropriateness and volume of referral between groups for the first ten MoleMate consultations of each Lead Clinician's data collection when contamination would be minimal ('naive period'), with the remaining consultations ('potentially contaminated period').

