### 2.4 Setting

Fifteen general practices are participating in the trial: thirteen in Cambridgeshire, one in West Essex and one in Suffolk. Practices already using a MoleMate system have been excluded. Two Lead Clinicians per practice have undergone training in the use and interpretation of the MoleMate system, and in all study procedures. GPs with known dermatological expertise eg GPs with a special interest (GPSI), Hospital Practitioners and Clinical Assistants in Dermatology, were excluded from being Lead Clinicians.

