#### Intervention group

Prior to commencing patient recruitment, Lead Clinicians complete a MoleMate Training CD-rom which teaches users to identify relevant SIAscopic features of various pigmented skin lesions. The Training CD-rom takes up to 2 hours to complete and has been shown to significantly improve GPs' ability to interpret SIAscopic images [22]. Participants in the intervention arm have their lesion/s assessed according to the same 'best practice' principles in the comparison arm. Lead Clinicians then use the MoleMate system to support their assessment and management of the lesion.

For all lesions an Index of Suspicion scale is completed, and the clinical diagnosis and intended action recorded (suspicious and refer via the two-week cancer route, or benign and reassure). A digital photograph is taken of every lesion for expert review.

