##### 3. Clinician outcomes

Continuous outcomes at the level of clinician such as confidence and attitudes, and change in these, towards the MoleMate system will be summarised using a mean score and 95% confidence interval and reporting the proportion of clinicians above a threshold of adequate confidence.

Assessment for learning effects will be undertaken using randomised comparisons of differences in proportions across 'naive' and 'potentially contaminated' periods: if there is an improvement in performance in the comparison arm and the intervention effect size becomes smaller through Lead Clinicians' sequence of lesions assessed, and this is a systematic effect established across the study clinicians, this would be evidence of either a learning effect or more general contamination.

The diagnostic performance of the seven-point checklist and the Index of Suspicion scale will be assessed and compared between the intervention and comparison groups.

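### The learning-effects check treats a post-training period as 'naive': it can show only contamination that builds with use, and its PPV contrast is too imprecise for a null result to mean no contamination

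*Protocol article*

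**What the plan says.** Section 2.9.2 (Clinician outcomes, Learning effects) accepts that "the MoleMate training programme, and using the MoleMate system in practice, may improve the Lead Clinicians' accuracy to assess pigmented lesions clinically", and that this could alter management in both groups. So it names two routes: training, and use of the device. The proposed check consists of "comparing the appropriateness and volume of referral between groups for the first ten MoleMate consultations" of each Lead Clinician, and then for the rest. The first ten are labelled naive, with contamination described as minimal. All later consultations are labelled potentially contaminated.

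Section 2.6 (Intervention group) fixes the timing of training: "Prior to commencing patient recruitment, Lead Clinicians complete a MoleMate Training CD-rom". Section 2.4 adds that "Two Lead Clinicians per practice have undergone training in the use and interpretation of the MoleMate system" and that "Fifteen general practices are participating in the trial", which gives 30 clinicians.

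Section 2.11 (Clinician outcomes) gives the interpretation. There is evidence of a learning effect or contamination "if there is an improvement in performance in the comparison arm and the intervention effect size becomes smaller" over the clinician's sequence of lesions, provided the effect is systematic across clinicians. No power or precision is stated for the check.

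**The concern.** Randomisation is by patient and stratified by Lead Clinician (section 2.3), so the same clinicians assess both arms. If the comparison arm improves because its clinicians have been trained on, or are using, the MoleMate system, the measured effect on the primary outcome shrinks. This check is the article's stated means of looking for that.

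There are three difficulties. First, a period that begins after training is not naive to training, so one of the two named routes lies outside what the contrast can show. Second, a cut at ten consultations may put a large share of the trial in the naive period, and more so since the target fell from 1,800 to 1,150. Third, the contrast is a difference of differences within the referred sample, which was sized only for the main comparison. A null result could be taken as reassurance that it does not provide.

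**Working it through.** **Inputs.** 15 practices with two Lead Clinicians each, so 30 clinicians (2.4). From 2.10: 1,150 randomised (originally 1,800), 400 referred lesions, 45% versus 60%, 80% power, 5% level, and at the interim 239 referred participants among 747 randomised. Assumed, because not stated: 1:1 allocation, a two-sided test, even recruitment across clinicians, and referrals split between periods in proportion to participants.

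**The plan's own figures.** n per arm = [1.96√(2p̄(1−p̄)) + 0.842√(p₁q₁+p₂q₂)]² / (p₁−p₂)².
- 12% versus 22%: 221 per arm, 442 in total, as stated.
- 45% versus 60%: 173 per arm, 346 in total; 372 with continuity correction; 372 × 1.06 = 394, close to the stated 400.

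**Timing of training.** Write early contamination as T + U₁ and late contamination as T + U₂, where T comes from training before recruitment and U from use. Late minus early is U₂ − U₁. T cancels, whatever its size.

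**Share of data labelled naive.**
- At 1,150: 1,150/30 = 38.3 participants per clinician, 19.2 in the MoleMate arm; 10/19.2 = 52%.
- At 1,800: 60 per clinician, 30 in the MoleMate arm; 10/30 = 33%.
- At 1,150, if the ten are counted across both arms: 10/38.3 = 26%.
- A clinician with fewer than ten MoleMate consultations adds fewer than ten to the naive total, so uneven recruitment lowers the 52%. It also leaves the later period weighted towards high recruiters.

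**Power of the PPV contrast.** With 200 referred lesions per arm, the cells are 200 × 0.522 = 104 early and 96 late. Taking p = 0.5:
- SE = √[0.25 × (2/104.3 + 2/95.7)] = 0.100, so the 95% interval is about ±20 points.
- Abrupt loss of all 15 points: Φ(0.15/0.100 − 1.96) = 32% (31% with a design effect of 1.06).
- Loss of half, 7.5 points: about 11%.
- Change detectable with 80% power: 2.80 × 0.100 = 28 points. About 1,395 referred lesions would be needed for 15 points.
- Under the 26% reading: cells of 52 and 148, SE 0.114, power 26%.

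**Other parts of the check.**
- Volume uses all participants: p = 239/747 = 0.32, cells of 300 and 275 per arm, SE = √[0.32 × 0.68 × (2/300 + 2/275)] = 0.055. Power is 78% for 15 points and 44% for 10 points.
- Comparison-arm PPV alone, early versus late, 45% to 60%: about 56%.

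**What the split loses.** Take 19 MoleMate consultations per clinician, with prior uses 0 to 18. The squared correlation between the early/late indicator and a linear trend is 0.75, so the split discards about 25% of the information. For a log trend the loss is about 41–44%, depending on how the count is set up. If the 15-point effect fades linearly to zero, the mean loss is 15 × 4.5/18 = 3.75 points in the first ten and 15 × 14/18 = 11.67 in the last nine. The split then sees 7.9 points against an SE of 10. Over the two trend shapes, power for gradual fading is roughly 8–12% with the split and 12–15% with a matching continuous model.

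**The case against.** The strongest reply is that the check does address something real. A reader might infer from the timing of training that it cannot detect contamination at all. The documents do not support that. Use of the system is the second named route, build-up with use is what an early-versus-late contrast targets, and the article calls early contamination minimal rather than absent. Nor should 32% be taken as the power of the whole check. It applies to PPV only; volume and the within-arm comparison do better.

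Other parts of the reply also stand. The training result cited in 2.6 concerns reading SIAscopic images, which comparison patients do not have, so it does not show that training changes comparison-arm decisions; 2.9.2 says only that it may. The 52% depends on even recruitment and is a ceiling under that reading of the ten. A reader might say that the first ten consultations hold most of the learning, but the article gives no learning curve. A reader might also put a chance rate on the 2.11 pattern from its first two conditions, but that would ignore the third, consistency across clinicians. How that condition is judged, and whether there is a formal interaction test, may properly sit in an analysis plan that is not shown. Section 2.11 already refers to the sequence of lesions, and nowhere says that a null check means no contamination.

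None of this restores the naive label with respect to training, or makes the PPV contrast precise.

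**Conclusion.** The point holds in a limited form. Sections 2.4 and 2.6 place training before the first patient, so describing the first ten consultations as minimally contaminated is inconsistent with naming training as a source in 2.9.2. The contrast can detect only contamination that grows with use. For PPV it does so weakly: about 32% power for complete, abrupt loss of the target effect, 26% under the alternative reading of the ten, and less for gradual loss. A null PPV contrast is therefore compatible with substantial contamination. The volume contrast is better, at about 78% for 15 points, but it measures a different outcome.

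The figures rest on 1:1 allocation, even recruitment over 30 clinicians, a two-sided 5% test and 400 referred lesions. The conclusion on training needs none of these. The primary analysis is not altered; what needs correcting is the inference drawn about contamination.

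**What to change.** State in 2.9.2 that any contamination from training is common to both periods and cannot be estimated in this trial, and that comparison-arm improvement arising from it would bias the result towards no effect.

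Replace the cut at ten. For each consultation in both arms, record the Lead Clinician's number of prior MoleMate uses. Model this with an arm interaction, for example through log(1 + prior uses) with a linear form as sensitivity analysis, allowing for Lead Clinician. Report the comparison-arm slope and the interaction with 95% confidence intervals, for PPV and for volume. Base any statement about contamination on those intervals.

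The cost is a change of wording in the analysis: consultation order is already needed for the planned check. The drawbacks are that a trend shape has to be assumed and that power for PPV stays low. The gain is a clearer limit on what may be concluded, and use of information that the split discards.

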##### Patient outcomes

Participants will complete the following psychological measures within 1 week and at 3 months after their consultation with the Lead Clinician:

- General and cancer-specific worry: Anxiety using the Spielberger State-Trait Anxiety Inventory, STAI [24] and a modified cancer worry scale [25];

- Satisfaction with the trial consultation using dimensions of care items from Europep [26].

##### Resource use and costs

The cost of the MoleMate system to the NHS will be assessed using the following data: costs of the MoleMate system (purchase, maintenance and technical support, staff training), costs of primary care activity (initial and diagnostic GP visits), and costs of secondary care activity (referrals, excision).

### 2.10 Sample size

Our pilot study confirmed projected recruitment rates (6-8 participants per practice per month) and referral rates (approximately 2 referrals per practice per month). Based on these, to detect an increased biopsy rate of 10% amongst those referred of 22% ('intervention' group) versus 12% ('comparison' group), an odds ratio of 2.0, with 80% power at the 5% significance level, would require 442 analysed in the primary outcome sample of referred lesions. With the involvement of 15 practices, this would require 30 referred lesions per practice. Assuming a 25% referral rate this could be achieved by randomising 120 patients per practice (1800 total) with an assumed recruitment rate of 90 per year over a 16-month period.

A blinded interim analysis, presented at the Trial Steering Committee meeting half-way through the study (September 2009) after 747 participants had been randomised, established a lesion referral rate of 28% (254/913), a mean cluster size amongst the referred sample of 1.06 (254 lesions from 239 participants), and that 55% of the referred lesions were assessed by the dermatology experts to be 'clinically significant' in the combined arm data. In this context of a higher rate of biopsy or monitoring, the clinically worthwhile difference was altered to a 15% difference (an odds ratio of 1.8) from 45% to 60%. A target total of 400 referred lesions from approximately 380 patients would provide 80% power to detect this difference at the 5% level of significance, and would require an estimated 1450 study lesions from 1150 randomised participants.

### 2.11 Analysis

#### Primary outcome (PPV of referral)

Analysis will be by intention-to-treat using the referred population for the primary outcome (i.e. all lesions referred to secondary care). The proportion of all referred lesions that are deemed 'clinically significant' will be compared between randomised groups using Donner's test for clustered proportions via a linear mixed effects model with patient as a random term. A secondary analysis comparing the proportions (chi-squared test) without allowance for clustering will enable an assessment as to whether clustering makes any difference to the results. If there is no material difference the simple analysis without need of accounting for clustering will be reported.

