#### Secondary outcomes

##### 1. Related to the primary outcome

*1.1 Volume effects*

The volume of referrals will be measured by the percentage of randomised participants over the study period who are referred by Lead Clinicians to secondary care, and compared between randomised groups as a difference in proportions with 95% confidence interval for the difference, and using the chi-squared test.

*1.2 Sensitivity, specificity and negative predictive value of the decision not to refer*

Sensitivity, specificity and other study proportions of lesions will be analysed using the same approach as for the primary outcome measure. These data will be used to compare the PPV of a referral (the primary outcome), and the NPV (correct management of lesions not referred) which will provide important data around lesions which are incorrectly identified as not suspicious in general practice. These data can contribute to further development of the diagnostic algorithm embedded in the MoleMate system.

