##### 4. Patient outcomes

Continuous secondary outcomes at the participant level, such as anxiety, cancer worry, and satisfaction with the consultation will be compared using a t-test, assuming no clustering effects are identified. Analyses will be unadjusted cross-sectional comparisons between groups. Change over time will also be summarised, reporting means at baseline and mean changes between time-points.

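### The primary analysis can switch from the patient-clustered test to the unclustered chi-squared test after both results are seen

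*Protocol article*

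**What the plan says.** In section 2.11, under the primary outcome, the unit of analysis is the lesion and the population is "all lesions referred to secondary care". The arms are to be compared "using Donner's test for clustered proportions via a linear mixed effects model with patient as a random term". The text then adds "A secondary analysis comparing the proportions (chi-squared test) without allowance for clustering", which "will enable an assessment as to whether clustering makes any difference to the results". The paragraph ends with the reporting rule: "If there is no material difference the simple analysis without need of accounting for clustering will be reported".

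Under the secondary outcomes related to the primary one, sensitivity, specificity and other lesion proportions "will be analysed using the same approach as for the primary outcome measure", so the rule carries over to them.

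Section 2.10 shows that the clustering exists. The blinded interim data gave 254 referred lesions from 239 participants, a mean of 1.06 per participant. The revised target is 400 referred lesions from about 380 patients.

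**The concern.** The order of the two analyses is set and then made reversible. The clustered test is valid whether or not lesions within a patient are correlated. The chi-squared test is valid only if they are not. The plan allows the second to replace the first on a judgement made once both treatment comparisons are available.

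Three features make this a poor rule:

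- **Direction.** With positive within-patient correlation the chi-squared test understates the variance, so the substitution tends to favour significance.
- **Weak evidence.** Agreement between the two results says little about whether correlation is absent. At the interim at most 15 patients (254 − 239) could have had more than one referred lesion, so the correlation would be poorly estimated. With so few multiple-lesion patients the two results will usually look alike, and the rule will usually select the simple analysis.
- **Timing.** The choice is most open to challenge when the primary result lies close to 0.05.

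**Working it through.** **Inputs.** From section 2.10: 254 referred lesions from 239 participants; target of 400 lesions from about 380 patients; revised effect 45% versus 60%; 80% power; 5% level. The document does not give the ICC, the distribution of lesions per patient or the sidedness of the test. I assume a two-sided test and ICC values from 0.1 to 1.0. The base case has extra lesions in pairs (no patient with more than two).

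**The plan's own figures.** Mean cluster size: 254/239 = 1.063, as stated. The revised target also reproduces approximately. The two-proportion formula with continuity correction gives 186 per arm, or 372 in total, and 372 × 1.06 = 394 lesions, close to the stated 380 patients and 400 lesions. Without the continuity correction the total is 2 × 173 = 346.

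**Size of a chi-squared test that is always reported.**

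- Effective cluster size = Σm²/Σm. With 224 patients having one lesion and 15 having two: (224 + 15 × 4)/254 = 284/254 = 1.118.
- Design effect DE = 1 + (1.118 − 1) × ICC.
- True two-sided size = 2[1 − Φ(1.96/√DE)].

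| ICC (assumed) | DE | True size |
|---|---|---|
| 0.1 | 1.012 | 5.1% |
| 0.3 | 1.035 | 5.4% |
| 0.5 | 1.059 | 5.7% |
| 1.0 | 1.118 | 6.4% |

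At the target of 400 lesions from 380 patients (360 with one, 20 with two), the effective cluster size is 440/400 = 1.10 and the size runs from 5.1% to 6.2%. If the 15 extra lesions instead sat in five patients with four each, the effective size is (234 + 5 × 16)/254 = 1.236 and the range is 5.3% to 7.8%.

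**A borderline example.** At DE = 1.059, a chi-squared p of 0.045 (z = 2.005) becomes z = 2.005/√1.059 = 1.948, so p = 0.051.

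**How often the two tests part.** I simulated 380 patients and 400 lesions, with a true proportion of 55% in both arms and 8,000 null trials per scenario. With extra lesions in pairs, the chi-squared and Donner tests disagreed on significance in about 0.1% to 1.1% of trials (ICC 0 to 1). In a harsher case, five patients with five lesions each and ICC 1, they disagreed in 2.8%. I then applied the switching rule with an assumed threshold, reporting chi-squared if the p-values differ by less than 0.01. With pairs and ICC 0.5, the rule rejected in 5.4% of trials, the same as the chi-squared test, against 4.7% for Donner's test (Monte Carlo standard error about 0.25 points). At ICC 1 the rule fell back to Donner's 5.1%, while the chi-squared test stood at 6.2%.

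**Cost of always keeping the clustered test.** For 45% versus 60% with 200 lesions per arm, power without clustering is 85.4%. With 200/DE per arm and DE from 1.01 to 1.10, it is 85% to 82%.

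**The case against.** The strongest reply is that the clustered test is named first and the switch operates only when the two analyses are judged alike. A change of significance is the plainest example of a material difference. If the team reads the rule that way, the reported verdict always equals the clustered verdict, the rejection rate is that of the clustered test, and only small differences in the printed p-value and interval remain. This largely stands, and it is why the effect is small. The text does not commit to that reading, though: 0.045 against 0.051 could be called immaterial in size or material in conclusion.

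A reader might also infer four stronger points that the document does not support.

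- **That the trial's type I error is 5.7% or 6.4%.** Those figures belong to a chi-squared test reported in every case. The rule reports it only in some.
- **That secondary proportions run at 7% or more.** Treating all 913 interim lesions from 747 participants as one denominator gives 7.1% to 7.6% at ICC 0.5, but no planned endpoint has that denominator. Sensitivity uses reference-positive lesions, specificity uses reference-negative ones, and NPV uses the non-referred (913 − 254 = 659). The cluster structure of these subsets is not given.
- **That the lack of a threshold for a material difference is itself a defect.** An analysis plan, which is not shown, may supply one. The criticism is of the rule's existence.
- **That the patient outcomes share the problem,** because they are "compared using a t-test, assuming no clustering effects are identified". Anxiety, worry and satisfaction are measured once per participant at each time point, so lesion clustering does not arise. Randomisation is individual and stratified by Lead Clinician (section 2.3). Ignoring a clinician effect common to both arms makes the t-test conservative, not anti-conservative. Adjusting for Lead Clinician would be a gain in precision only and is not part of this point.

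**Conclusion.** The point holds as a flaw in the reporting rule with a small numerical effect. The article states affirmatively that the unclustered result may replace the clustered primary one after both are known, and nothing elsewhere in it removes that rule. For the primary outcome, 5.1% to 6.4% is an upper guide to the true size. It rests on a two-sided 5% test, extra lesions in pairs and an ICC of 0.1 to 1.0; more concentrated lesions would raise it. The practical exposure is a primary result close to 0.05, where the choice of test could be disputed. For the secondary lesion proportions the effect could be larger, since all study lesions average 913/747 = 1.22 per participant, but the document does not allow it to be computed.

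**What to change.** Delete the switching sentence from section 2.11. State instead that the patient-clustered analysis is primary and will be reported whatever the chi-squared test shows, with the chi-squared result given only as a sensitivity analysis. Say that the same holds for sensitivity, specificity, NPV and the other lesion-level proportions. Make the change before the arms are compared.

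The cost is a sentence or two of wording. On the paired assumption, confidence intervals would be wider by a factor of √DE, between √1.012 = 1.006 and √1.118 = 1.057, so about 1% to 6%. The loss of power is that shown in the working, and it stays above the planned 80%.
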